## Abstract

**Background:**

Venous leg ulcers are common, chronic wounds that are painful and reduce quality of life. Compression therapy is known to assist in the healing of venous leg ulceration. Supervised exercise training that targets an improvement in calf muscle pump function might be a useful adjunctive therapy for enhancing ulcer healing and other aspects of physical and mental health. However, the evidence of exercise for individuals with venous ulcers is sparse. Here, we describe the protocol for a study that aims to assess the feasibility of undertaking a randomised controlled trial of a supervised exercise programme in people who are receiving compression for venous ulceration.

**Methods/Design:**

This is a randomised, controlled, assessor-blinded, two-centre, feasibility trial with two parallel groups. Eighty adults who are receiving lower-limb compression for a venous leg ulcer will be randomly assigned to receive usual care (compression only) or usual care plus a 12-week supervised exercise programme. Participants in the exercise group will be invited to undertake three, 60-minute sessions of supervised exercise each week, and each session will involve a combination of treadmill walking, upright cycling and strength and flexibility exercises for the lower limbs. Participants will be assessed before randomisation and 3, 6 and 12 months after randomisation. Primary outcomes include rates of recruitment, retention and adherence. Secondary outcomes include time to ulcer healing, proportion of participants healed, percentage and absolute change in ulcer size, health-related quality of life (EQ-5D-5L and VEINES-QOL/Sym), lower-limb cutaneous microvascular function (laser Doppler flowmetry coupled with iontophoresis) and physical fitness (30-second sit-to-stand test, chair sit and reach test, 6-minute walk test and ankle range of motion). The costs associated with the exercise programme and health-care utilisation will be calculated. We will also complete interviews with a sub-sample of participants to explore their experiences of having a venous ulcer and the acceptability of the exercise intervention and study procedures.

**Discussion:**

Data from this study will be used to refine the supervised exercise programme, investigate the acceptability of the intervention and study design and determine the most appropriate outcome measures, thereby providing estimates of the factors needed to design an adequately powered trial across several centres.

**Trial registration:**

Current Controlled Trials, ISRCTN10205425 (May 2014) - http://www.controlled-trials.com/ISRCTN10205425

**Electronic supplementary material:**

The online version of this article (doi:10.1186/s13063-015-0963-z) contains supplementary material, which is available to authorized users.

## Background

Venous ulceration is the most common type of leg ulceration. The occurrence of venous leg ulcers increases with age, and the annual UK prevalence in those over 65 years is estimated at 1.7 % [1]. Venous ulcers arise from venous valve incompetence and calf muscle pump insufficiency which leads to venous stasis and hypertension. This results in microcirculatory changes and localised tissue ischaemia [2, 3]. The natural history of the disease is of a continuous cycle of healing and breakdown over decades, and chronic venous leg ulcers are associated with considerable morbidity and impaired quality of life [4]. Treatment of this major health problem results in a considerable cost to the National Health Service (NHS). The cost of treating one ulcer was estimated to be between £1,493 and £1,795 per year on the basis of 2010–2011 prices and in the context of a trial conducted within the UK NHS [5].

A first-line treatment for venous ulcers is compression therapy, the objective of which is to provide graded external compression to the leg and oppose the hydrostatic forces of venous hypertension [6]. Cochrane reviews have concluded that compression therapy is effective for promoting ulcer healing [7] and reducing the risk of ulcer recurrence [8]. O’Meara and colleagues [7] also concluded that multi-component systems delivering high compression (defined as 40 mm Hg of compression at the ankle) were the most effective treatment for venous ulcers. A recent trial demonstrated that two-layer compression hosiery is equally effective as four-layer bandaging for the healing of venous ulcers [5].

Lifestyle factors, including nutrition, exercise and smoking, are also mentioned in guidelines on the management of venous ulceration and chronic venous insufficiency (CVI) [9]; however, these factors receive relatively little emphasis. Exercise training that targets an improvement in calf muscle pump function might be a particularly useful adjunct therapy for enhancing ulcer healing and other aspects of physical and mental health. Exercise training is routinely prescribed for other forms of cardiovascular disease such as peripheral arterial disease [10] and coronary artery disease [11]. In patients with venous leg ulcers, supervised calf muscle exercise has been shown to increase calf muscle pump function and improve lower-limb haemodynamics [12, 13], and supervised treadmill walking exercise has been shown to improve lower-limb skin microvascular function in individuals with mild CVI [14]. However, a recent systematic review concluded that further research is required to determine whether exercise training has a beneficial effect on ulcer healing and health-related quality of life [15].

In light of this background evidence, we hypothesised that a specially designed supervised exercise programme delivered in conjunction with compression therapy would be a more effective means of promoting venous ulcer healing than compression therapy alone. Before embarking on an adequately powered randomised trial to test this hypothesis, we have planned a preliminary study that will address several areas of uncertainty. For example, leg pain and the perception that exercise might be harmful or too difficult to perform have been identified as barriers to exercise in people with venous ulcers [16], and this raises questions about how easy it will be to recruit and retain participants in a trial of a supervised exercise programme. The specific aims of the present feasibility study are the following:Estimate the rates of recruitment and retention for a future definitive trial of a 12-week supervised exercise programmeEstimate the rates of attendance to and compliance with the supervised exercise programmeEstimate the outcome completion rate (provision of data) immediately after the intervention ends and at 12 months after randomisation to identify any potential differences in completion between those randomly assigned to exercise and those randomly assigned to controlIdentify a primary outcome and estimate the sample size for a subsequent definitive trialRefine a framework to facilitate conducting a cost-effectiveness analysis of the interventionConduct post-intervention interviews with participants to refine the design and delivery of the supervised exercise programme.

## Methods/Design

### Study design

The FISCU (Feasibility of Implementing Supervised exercise training alongside Compression therapy in people with venous Ulceration) study is a mixed methods feasibility study involving an exploratory randomised controlled trial with a nested qualitative component. Eighty adults who are receiving lower-limb compression for a new venous ulcer will be randomly assigned 1:1 to receive usual care (compression only) or usual care plus a 12-week supervised exercise programme. Participants will be followed up until 12 months after randomisation. The study is being run across two centres: Sheffield and Lincoln, UK. The study is registered with the International Standard Randomized Control Trial Number Register (ISRCTN10205425) while the study protocol conforms to the Spirit Checklist (Additional file 1).

This study started in May 2014 and is due to last until May 2017. The trial is sponsored by the Sheffield Health and Social Care NHS Foundation Trust, and ethical approval was granted by the NHS National Research Ethics Service, Yorkshire and the Humber (Sheffield) Committee (14/YH/0091), which co-ordinates ethical permissions across the following study and recruitment sites:Sheffield Hallam UniversitySheffield Health and Social Care NHS Foundation TrustSheffield Teaching Hospitals NHS Foundation TrustSheffield Clinical Commissioning GroupUniversity of LincolnLincolnshire Community Health Services NHS Trust.

### Recruitment of participants

In both Sheffield and Lincoln, participants will be recruited from community nursing and tissue viability teams or services, family doctor practices, community and outpatient leg ulcer clinics, and wound clinics. The primary mode of identifying potentially eligible patients will be through the weekly screening of primary care-based electronic record systems by practice nurses, tissue viability nurses, or specially trained administrators. Poster advertisements will also be used.

Eligible individuals will be sent an invitation letter, a brochure about the study, containing an invitation letter (including the contact details of a research team member), and a reply slip. For those recruited directly from primary care, the invitation letters are sent by the primary care practice where the search was conducted. For those recruited from existing databases, the invitation is sent from the chief investigator. Individuals who are interested in taking part are asked to return a reply slip directly to the FISCU research team. Patients who satisfy telephone pre-screening will be invited to the Centre for Sport and Exercise Science at Sheffield Hallam University or the Human Performance Centre at the University of Lincoln for their first formal study visit, during which they will be habituated with the trial, provide written informed consent (obtained by a research assistant or clinician), be confirmed for eligibility by a clinician, and complete baseline assessments.

### Eligibility criteria

Patients are eligible for the trial if they:are at least 18 years of agehave at least one venous leg ulcer of primarily venous aetiology (determined by a clinician) with a maximum diameter of  at least 1 cmhave an ankle brachial pressure index (ABPI) of at least 0.8 (recorded within the previous 3 months)are able and willing to tolerate lower-limb compression.

Patients are excluded from the trial if they:are unsuitable or unable to exercise (determined by a clinician)are unable or unwilling to tolerate lower-limb compressionhave insulin-controlled diabetes mellitusare pregnanthave coexisting skin conditions, vasculitis, deep venous occlusion or malignant/atypical ulcerationrequire major surgeryhave a leg ulcer with a maximum diameter of less than 1 cmhave had an ulcer at the same site within the previous 3 monthsare unable or do not wish to consent to participation in the trial.

### Baseline measurements

In visit 1, after written informed consent has been obtained and eligibility confirmed (which will include a medical examination), the following baseline measurements will be recorded:demographic data, including age, sex, and socioeconomic statusclinical history, including incident or recurrent ulcer, duration of ulcer disease, duration of current ulcer (oldest ulcer and reference ulcer if different), previous operations, comorbidities, current medications, height, weight, ankle and calf circumferenceulcer size: measurement of ulcer size will involve taking a leg ulcer tracing by using a fine-nibbed indelible pen onto a conformable acetate film with a pre-printed grid. When a participant has multiple venous ulcers, all ulcers will be traced, and the eligible ulcer with the largest surface area will be deemed the reference ulcer for the trial. The reference ulcer and any other ulcers will be drawn onto a leg diagram. A digital image of the reference ulcer will also be taken.ABPI: a Doppler-determined measurement of ABPI will be performed according to the procedures of Aboyans et al. [17] unless a reading of less than 3 months old has been obtained from clinical records.baseline exercise historyhealth status: EQ-5D-5L [18]disease-specific quality of life and symptoms: VEINES-QOL/Sym [19]lower-limb cutaneous microvascular function (see Outcome Measures section for detailed description) [14, 20]physical fitness, using three items from the Senior Fitness Test (see Outcome Measures section for detailed description) [21] and ankle range of motion assessed by using a bi-plane ankle goniometer (maximum dorsiflexion through to maximum plantarflexion).

### Randomisation and masking

After completion of baseline assessments, participants will be randomly assigned 1:1 to an intervention group or a control group. The research assistant will request (via email) a participant’s allocation from the trial statistician (AG) who manages the randomisation schedule. The statistician is not involved in the recruitment or data-gathering processes and is based in a different location to where the study visits are completed. Participants will be stratified by ulcer size (maximum ulcer diameter of either between 1 and 3 cm or greater than 3 cm in any direction) with permuted blocks of variable size, because this criterion is a known predictor of ulcer healing [22]. We could not mask participants or intervention supervisors to the allocated treatment. Outcome assessors will be blinded to group allocation.

### Withdrawals

Participants will be considered to be withdrawn from the trial if they request to leave the trial, if they are lost to follow-up, or if they die before completing the 12-month follow-up. Participants will be considered to be withdrawn from the allocated treatment if they no longer receive the supervised exercise training if allocated to the exercise group or if they no longer receive compression therapy regardless of which group they are in. Treating nurses will be asked to keep the participant with their original compression therapy (i.e., bandaging or stockings) unless there are objective clinical reasons for changing. Withdrawals from the trial and from the allocated treatment will be included in the analysis by intention-to-treat.

### Supervised exercise programme

A description of the supervised exercise programme is provided separately (Additional file 2). Participants allocated to the intervention group will be invited to attend three sessions of supervised exercise each week for 12 weeks (total of 36 sessions) at one of the two study exercise training facilities (Sheffield Hallam University and University of Lincoln). Sessions will typically be delivered on Mondays, Wednesdays and Fridays to allow sufficient recovery between sessions, although the weekly training structure will be flexible to work around participants’ commitments. The 12-week programme duration was chosen on the basis of a median ulcer healing time of 9 to 11 weeks for patients receiving compression therapy [23]. Sessions will be performed in the late morning, afternoon or early evening, given the higher occurrence of adverse cardiovascular events during early-morning exercise [24]. A maximum of 14 weeks will be allowed for the participants to complete the 36 sessions in case sessions are missed because of, for example, illness or holiday.

Each exercise session will last approximately 60 minutes and will comprise a combination of aerobic, resistance and flexibility exercises. Each session will begin and end with 5 minutes of low-intensity treadmill walking or cycling for a warm-up and cool-down, respectively. The aerobic component will last approximately 30 minutes, and whether the exercise mode is treadmill walking, cycling, or a combination of both is determined by the physical function and preference of participants. Treadmill hill-walking will be the preferred mode since it promotes greater recruitment of the calf musculature than cycling. The intensity will be moderate and this is due to evidence that moderate-intensity exercise training improves cardiorespiratory fitness, cardiovascular health, venous vascular function and skin microvascular function [14, 25, 26] and the fact that it will likely be better tolerated than high-intensity exercise. The intensity of exercise will be guided by the use of Borg’s 6- to 20-point exertion scale [27]; participants will exercise at an exertion level of 12 to 14 (somewhat hard), which equates to the ventilatory threshold [28]. The use of relative intensities will ensure that the exercise programme has inherent progression as the participants become fitter. Perceived exertion, heart rate (via telemetry) and exercise settings (e.g., treadmill speed and gradient) will be recorded at 5-minute intervals during aerobic training to allow accurate quantification of the exercise stimulus and progression of the programme over time.

Resistance and flexibility exercises will be performed for approximately 20 minutes in order to improve calf muscle pump function, leg (predominantly calf) muscle strength, and joint (predominantly ankle) mobility. Resistance exercises will predominantly involve dynamic body-weight exercises with or without the use of dumbbells and stability balls (e.g., calf raises and partial squats). Exercise will be performed for two or three sets of 10 to 15 repetitions to the point of moderate muscle fatigue [29]. For flexibility, static stretches will be performed for all of the major muscle groups of the legs, for a total of 60 seconds per muscle group (comprising 3 × 20-second stretches), held at the point of mild discomfort [29].

A trained exercise physiologist will supervise each session, and there will be a maximum of four participants per session to help ensure patient safety, successful delivery of the exercise session and collection of data. Compression garments (stockings/bandages) will be monitored during each exercise session: if affected by exercise, participants will be referred to the tissue-viability nursing team for re-application, and additional visits will be noted for the health-economics analyses. An experienced clinical exercise physiologist (GT) will be responsible for ensuring treatment fidelity of the exercise programme at both training sites.

After the completion of the intervention period, all exercise group participants will receive a personalised leaflet including an exercise programme that they could manage on their own. Adherence to those instructions will be monitored at follow-up visits.

### Usual care

Participants from both groups will receive standard compression therapy directed by experienced tissue-viability nurses, according to their individual circumstances and following standard local practice (e.g., multi-layered compression bandaging or two-layer compression stockings as well as standard advice to elevate the affected leg). Patients will be reviewed in clinics as often as is deemed clinically necessary.

### Study outcomes

All staff of the respective trial sites have been trained on the study protocol, informed consent and assessment data collection procedures. Study-specific standard operating procedures have also been developed to help ensure consistent data collection procedures between different outcome assessors and sites. Outcome assessors will be blinded to group allocation.

Follow-up visits for assessment of outcome measures will be completed 3 months (i.e., soon after the end of the supervised exercise programme) and 12 months after randomisation. A postal questionnaire follow-up will also be conducted 6 months after randomisation.

### Feasibility outcomes

The main focus of this study is acceptability and feasibility of procedures for recruitment, allocation, measurement and retention and for the intervention procedures. Recruitment rates will be measured as rate of invited participants who are eligible and consenting and will be reported in a CONSORT (Consolidated Standards of Reporting Trials) participant flowchart. Acceptability of allocation procedures will be assessed by examining reasons for dropout in discontinuing participants and comparing attrition rates between the two study groups. Suitability of measurement procedures will be evaluated on the basis of completion rates and reasons for missing data. Attrition rates will be established as discontinuation of intervention and loss to follow-up measurement for all conditions. The acceptability of the exercise programmes will be assessed by using session attendance and compliance data and participant feedback via one-to-one semi-structured interviews conducted with a sub-group of participants after the 3-month follow-up visit. The safety of exercise training will also be assessed by exploring reasons for dropout from the exercise programme and the number and type of adverse events that occur in each group.

### Secondary outcomes

#### Time to reference ulcer healed

Healing will be defined as complete epithelialisation in the absence of scab/eschar. The treating nurse will inform a study investigator when the reference ulcer and last ulcer (if applicable) have healed. A digital photograph of the reference/last ulcer site will be taken for validation purposes at healing and 7 days after healing. These images will be assessed ‘blind’ for confirmation of healing.

#### Proportion of patients healed

The proportion of patients healed will be assessed 3, 6 and 12 months after randomisation. This will allow direct comparison with other trials.

#### Percentage and absolute change in ulcer size

Percentage and absolute change in ulcer size will be measured 3 and 12 months after randomisation. The data collected will allow the determination of reduction in ulcer area in patients who do not achieve complete ulcer healing. Measurement of ulcer size will involve tracing on acetate films, as described above.

#### Proportion of time patients are ulcer-free

Reduction in recurrence would help reduce the prevalence of this condition and thus cost. Crude recurrence rates are potentially biased by any difference in healing rates associated with the two groups (exercise or control) since if one group has more rapid healing, then people in that group are at risk of earlier recurrence. To account for this, we will use the proportion of time that patients are ulcer-free as the clinically important measure since it is a function of both healing and recurrence and it is important for patients. Recurrence data will be collected 3, 6 and 12 months after randomisation.

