### Statistical analysis

The sample size for a feasibility study should be adequate to estimate critical metrics, needed to assess the feasibility of conducting the definitive study, with sufficient precision. Herein, the critical metrics are the consent rate (i.e., the proportion of eligible patients who consent to participate and be randomly assigned), ulcer-healing rates and compliance with treatment, and attrition. Forty patients in each group will provide a sufficiently precise (within 15 percentage points for a 90 % CI) estimate of the proportion willing to be randomly assigned, assuming 35–40 % intention to be randomly assigned. A sample size for an adequately powered randomised controlled trial will be determined from the results of this trial.

Descriptive statistics will be used to characterise the groups at baseline and to present the feasibility outcomes described above. Although determining differences in clinical outcomes between the two arms is not the primary purpose of this trial, comparisons will be undertaken to investigate the feasibility of studying these outcomes and to calculate estimates for the likely effect sizes and 95 % CIs. Analyses will be conducted in SPSS by using the principles of intention-to-treat. Significance tests will be two-sided at the 5 % level. Healing rates will be compared by using the Kaplan-Meier method. Hazard ratios and 95 % CIs will be presented for ulcer healing time by using Cox regression analysis models. For other outcomes, the intervention and control groups will be compared by using linear or logistic regression (depending on the type of outcome) adjusting for ulcer size and any other important baseline covariate. Relevant assumptions will be checked for all models. For the potential primary outcomes for a definitive trial, the likely effect of the exercise intervention will be estimated via standard intervention minus control comparisons, accounting for the type of variable and its distributional properties. We will examine whether the CIs include potentially clinically important effects in outcomes between groups. As this is a feasibility study, these comparisons are exploratory and are intended to inform the subsequent, definitive trial.

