### Criteria for success

This feasibility trial will be deemed successful and lead to the development of a proposal for an adequately powered randomised controlled trial if:(i)An appropriate primary outcome variable is defined(ii)At least 67 % of randomly assigned patients in the exercise group are compliant with the intervention (defined as at least 75 % of the scheduled sessions are completed as planned)(iii) Loss to follow-up at 12 months is less than 20 %(iv) Patient preferences are not so strong that they result in the conclusion that a randomised controlled trial is not a feasible design.

The criteria for success will provide the basis for interpreting the results of this study and determine whether it is appropriate to proceed to a full trial and (if appropriate) what modifications need to occur for a full trial to be feasible.

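### Ulcer-free time is sent to ordinary regression with trial withdrawals included, so shortened follow-up lowers the score on average and unequal withdrawal would bias the comparison between arms

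*Protocol article*

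**What the plan says.** All places are in the protocol article.

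- **Eligibility criteria.** Every participant has at least one venous ulcer at entry.
- **Proportion of time patients are ulcer-free.** Crude recurrence rates are rejected because faster healing exposes a group to earlier recurrence. Instead "we will use the proportion of time that patients are ulcer-free as the clinically important measure". The section gives neither the denominator nor a rule for time after someone leaves.
- **Study design.** "Participants will be followed up until 12 months after randomisation".
- **Withdrawals.** Trial withdrawal is defined by three events: "if they request to leave the trial, if they are lost to follow-up, or if they die before completing the 12-month follow-up". Withdrawal from the allocated treatment is a separate category. For both, "Withdrawals from the trial and from the allocated treatment will be included in the analysis by intention-to-treat".
- **Statistical analysis.** Kaplan-Meier and Cox methods are named for healing. "For other outcomes, the intervention and control groups will be compared by using linear or logistic regression (depending on the type of outcome"), with adjustment for ulcer size. The clinical comparisons are described as exploratory.
- **Time to reference ulcer healed.** "The treating nurse will inform a study investigator when the reference ulcer and last ulcer (if applicable) have healed". This report does not depend on a study visit.
- **Incremental cost-effectiveness ratio.** Imputation of missing data is mentioned here, for the economic analysis only.

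**The concern.** The measure was chosen to remove one bias between arms, but as written it is open to another. Each person starts in the ulcerated state and can gain ulcer-free time only after healing, so the expected proportion rises with the length of follow-up. Someone observed for three months will usually score well below what the same person would score over twelve. Linear or logistic regression of each person's proportion takes no account of this. If withdrawal from the trial differs between arms, the arm that loses more people looks worse with no true difference in healing or recurrence.

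Unequal loss is a possibility that the article itself wants examined: the aims include looking for differences in data completion between groups, and the feasibility outcomes include comparing attrition by group. At stake is the effect estimate for this outcome, which is meant to inform the design of the definitive trial.

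**Working it through.** The article gives no figure for this outcome, so there is none to reproduce.

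**Inputs from the article.** Follow-up is 12 months, taken as 52 weeks. Healing: "a median ulcer healing time of 9 to 11 weeks for patients receiving compression therapy". The ulcer is open at time zero.

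**Assumed inputs (not in the article).** Healing times are exponential. Recurrence is 0, 25 or 50 % per year. Withdrawal is unrelated to healing, at 20 % in one arm and 5 % in the other. There is no treatment effect.

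**1. One person.** Healing is at week 10, with no recurrence. Followed to week 52, the score is 42/52 = 0.81.

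| Leaves at week | Observed-time denominator | Fixed 52 weeks, unobserved time not ulcer-free |
|---|---|---|
| 8 | 0 | 0 |
| 12 | 2/12 = 0.17 | 2/52 = 0.04 |
| 26 | 16/26 = 0.62 | 16/52 = 0.31 |

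**2. Closed form, no recurrence.** With healing rate k, the mean proportion over follow-up T is 1 - (1 - exp(-kT))/(kT). At a median of 10 weeks, k = ln 2/10 = 0.0693 per week.

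- T = 52: kT = 3.604, mean 1 - 0.973/3.604 = 0.73.
- T = 13: kT = 0.901, mean 1 - 0.594/0.901 = 0.34.

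If 15 percentage points more of one arm leave at week 13, the false difference is -0.15 × (0.730 - 0.341) = -5.8 points on observed time. On a fixed 52 weeks a leaver scores 0.341 × 13/52 = 0.085, which gives -0.15 × (0.730 - 0.085) = -9.7 points.

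As a yardstick, an assumed true healing hazard ratio of 1.25 raises k to 0.0866 and the 52-week mean to 0.78, a gain of 5.0 points.

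**3. Simulation with recurrence.** 400,000 patients per setting, median healing 9 or 11 weeks, recurrence 0 to 50 % per year, withdrawal 20 % versus 5 %, no true effect.

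| Timing of departures | Observed time | Fixed 52 weeks |
|---|---|---|
| Uniform over the year | -3.1 to -3.7 points | -5.5 to -6.6 points |
| Uniform over weeks 0 to 12 | about -7 to -8.5 points | about -9 to -11 points |

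On observed time, leavers spread over the year average 0.42 to 0.51, against 0.62 to 0.76 had they been followed in full. Leavers in weeks 0 to 12 average 0.16 to 0.19. When withdrawal is equal in number and timing and healing is equal, both arms are pulled down alike and the false difference is near zero.

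**4. Not every leaver is affected.** On observed time, about 2 to 4 % of leavers (those not healed by week 52) score 0 either way. With recurrence of 25 to 50 % per year, about 2 to 12 % score higher than their full-year value, because they leave before a recurrence.

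**5. Would the success criteria catch it?** One criterion is "Loss to follow-up at 12 months is less than 20" %. With equal allocation, 20 % and 5 % average (20 + 5)/2 = 12.5 %. If the criterion is read across both arms, the trial would pass it with this bias present.

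**The case against.** The strongest reply is that no formula is stated. The article gives neither a denominator nor a rule for time after withdrawal. It promises that model assumptions will be checked, and a full protocol or analysis plan could settle the rest. This stands in part: a missing denominator in an article is no fault by itself. But the article does assign a class of model. It reserves censoring methods for healing and sends other outcomes to regression, with trial withdrawals included. Both natural denominators are biased in the same direction, so leaving the denominator open does not rescue the plan.

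A second reply is that data already arrive without visits: nurse reports of healing, a postal questionnaire at 6 months and weekly telephone calls. These help, but nothing says that they continue once a person is withdrawn from the trial, and they do not change the analysis.

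A third is scale, and this stands. The withdrawal and recurrence rates are assumed, and a smaller gap gives a smaller bias. At 40 per arm, with the simulated SD of 0.274 (median 11 weeks, 50 % recurrence), the 95 % half-width is 1.96 × 0.274 × √(2/40) = 12 points, well above a bias of 3 to 4.

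A reader might also infer more than the text supports:

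- That anyone who leaves scores too low. This is true only on average.
- That the burden of 36 sessions must distort the result. Someone who stops only the exercise is withdrawn from treatment, stays in follow-up and loses no observed time.
- That missed visits count as withdrawal. The section lists a request to leave, loss to follow-up and death.
- That the article expects more loss in the exercise arm. It sets out to look for differences and predicts none.
- That this outcome is a named candidate for the definitive trial's primary outcome. No section says so.

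**Conclusion.** The concern holds in a limited form. As written, ulcer-free time is analysed by a method that ignores length of follow-up, with trial withdrawals included. Unequal withdrawal from the trial would bias the comparison against the arm that loses more people, even when leaving is unrelated to healing. The direction follows from the open ulcer at entry. The size rests on the assumed 15-point gap in withdrawal, on exponential healing at the article's medians and on the assumed recurrence range. Within those limits the bias for departures spread over the year is smaller than, or not much larger than, the effect of a healing hazard ratio of 1.25, and early departures could cancel such an effect. Because the comparison is exploratory and no success criterion rests on it, the consequence is a distorted effect estimate passed to the definitive trial. The feasibility conclusions themselves are not put in doubt.

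**What to change.** 1. **Proportion of time patients are ulcer-free, and Statistical analysis.** Define the outcome as ulcer-free time over a fixed 12-month window from randomisation. Estimate it by arm with a method that handles censoring: the area between the healing and recurrence curves, a multi-state model, or multiple imputation of the unobserved months. Imputation would let the stated regression with adjustment for ulcer size stand. Do not regress each person's crude proportion. Say separately how time after death counts, since it is not simply unobserved.
2. **Withdrawals.** Distinguish people who stop study visits from people who refuse further data. For the former, with consent, keep collecting nurse-reported healing and recurrence dates to month 12.

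The first change assumes that those who leave resemble those who stay, given what is modelled. The second reduces reliance on that assumption, and an analysis plan cannot supply it afterwards. The cost is wording in three sections, a short consent clause and slightly more analysis. No extra visits are needed, and recruitment is described as ongoing, so the change is still useful.
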